
### Interim analyses {21b}

No interim analyses are planned at this moment. However, the trial steering group can request interim analysis at any time. In this case, the analysis will be performed by one of the main researchers and results will be discussed with the trial steering group.

### Methods for additional analyses (e.g., subgroup analyses) {20b}

Described above, under SPIRIT item {20a}.

### Methods in analysis to handle protocol non-adherence and any statistical methods to handle missing data {20c}

Described above, under SPIRIT item {20a}.

### Plans to give access to the full protocol, participant-level data, and statistical code {31c}

N/a—The full trial protocol will be available at ClinicalTrials.gov and upon publication of this protocol paper. The de-identified dataset will be made publicly available upon publication of the study results via KU Leuven Research Data Repository.

## Oversight and monitoring

### Composition of the coordinating center and trial steering committee {5d}

Different working groups have been established to organize the design, execution, and follow-up of this intervention study. Table 3 provides an overview of the composition, roles, and responsibilities and meeting frequency of the involved working groups.

**Table 3 Tab3:** Schematic overview of the composition, roles and responsibilities, and meeting frequency of the working groups providing trial support

	**Composition**	**Roles and responsibilities**	**Meeting frequency**
**Trial steering group**	Day-to-day management team, child neurologist, child orthopedic surgeon, experts in the field of (pediatric) rehabilitation	- Agreement on final protocol - Reviewing study progress and if necessary agreeing on changes to the protocol - Assistance in patient recruitment - Data analysis and interpretation - Reporting of trial results to relevant parties - Advice on publicity and presentation of all aspects of the trial	Three times a year
**Day-to-day management team**	Principle investigator and main researchers	- Study planning and coordination (e.g., communication between involved parties) - Budget administration - Initial preparation and revisions of the study protocol and related documents - Organization of meetings with the trial steering group - Clinical trial registration (e.g., ClinicalTrials.gov) - Trial conduct (e.g., scheduling therapy sessions, performance of eligibility screening, study logistics) - Recording and reporting of adverse events - Data quality assurance - Provision of annual progress report to the Ethics Committee Research UZ/KU Leuven	Monthly meetings
**Principal investigator**	Senior professor at KU Leuven	- Supervise trial conduct - Protect rights, safety and well-being of participants - Responsible for data storage and preservation	/
**Data management team**	Main researchers	- Build trial specific database on REDCap platform - Data entry and verification	Monthly meetings
**Stakeholders**	Physiotherapists working in private practices across Flanders and children and adolescents with unilateral cerebral palsy and their parents	- Advice on study protocol (e.g., therapy intensity, duration of therapy and assessment sessions) - Discussions on strengths/weaknesses/opportunities/threats of this study	Occasional video-meetings

### Composition of the data monitoring committee, its role and reporting structure {21a}

N/a—No data monitoring committee will be composed for this trial because of the activity-based character of the therapy and assessments, which have shown to be safe in earlier studies.

### Adverse event reporting and harms {22}

Information regarding adverse events will be collected from the participants and their parents through in-person conversations during each participant contact. According to the regulations of the Ethics Committee Research UZ/KU Leuven, all adverse events will be evaluated by the researchers as to seriousness, severity, and causality to the therapy or assessments. Depending on the severity of the adverse event, appropriate follow-up and reporting of these events will be organized by the researchers, and in consultation with the involved medical doctors.

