### Intervention description {11a}

Participants in both groups will receive three sessions of 45 minutes upper limb therapy per week for a period of eight weeks, resulting in a total therapy duration of 18 hours. All therapy sessions will be performed by individual physiotherapists or occupational therapists who have experience working with children with CP. The participant/therapist ratio will be 1:1 for both therapy groups.

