### Strategies to improve adherence to interventions {11c}

To evaluate compliance, therapists from both groups will be asked to record the frequency and duration of the effective therapy time and the executed exercises/activities. After the first week of intervention and halfway through the intervention period, parents and therapists will be contacted by one of the researchers to discuss the feasibility of the therapy and the progress the child has made.

Furthermore, for the intervention group, adherence of the therapists to the Sense for Kids therapy protocol will be scored using a fidelity checklist that contains all fundamental elements of the therapy and relevant implications regarding therapy receipt (Additional file 1) [58]. The fidelity checklist was audited by five researchers and clinicians who have experience with the provision of Sense for Kids therapy. Modifications were made to improve clarity of the necessary elements, include essential elements of occupational-based therapy and remove assessment items to confine the forms application to individual and subsequent Sense for Kids therapy sessions. Fidelity of three randomly selected therapy sessions of each participant will be assessed based on a video recording of the therapy session. All video recordings will be scored by an independent reviewer who has experience with the Sense for Kids therapy but is not involved in the provision of therapy within the scope of this study. Each criterion will be scored on a 4-point Likert scale and a percentage score will be computed to objectify adherence. A percentage score of 80% or higher will be considered as sufficient adherence to the therapy protocol.

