### Provisions for post-trial care {30}

N/a—After informed consent for the screening has been obtained until the last follow-up visit, all adverse events causally related to a study intervention will be reported according to the regulation of the Ethics Committee Research UZ/KU Leuven. Although adverse events and possible injuries are not expected due to the clinical nature of the study, participants are insured during their participation in all study-related interventions, including the assessments and therapy sessions, through the insurance taken by KU Leuven.

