### Plans to promote participant retention and complete follow-up {18b}

To avoid dropouts due to practical considerations, the scheduling of therapy and assessment sessions will be adapted to the participant’s preferences where possible. Furthermore, one contact person will be appointed to coordinate the scheduling of therapy and assessments and to resolve any questions. Lastly, parents will be contacted after the first week of therapy and halfway the intervention period to discuss feasibility of the therapy and the progress the child has made. In case of deviations from the study protocol (e.g., missed therapy sessions due to illness), the assessments will still be scheduled as described above and the specific deviation will be noted.

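### The treating therapists have no stated role in adverse event collection, and the plan does not fix how soon an event during therapy is asked about

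*Protocol article*

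**What the plan says.** The section Adverse event reporting and harms {22} fixes three things: the source (participants and parents), the mode (conversation in person) and the occasion (each contact). Information is "collected from the participants and their parents through in-person conversations during each participant contact". The researchers then judge seriousness, severity and causality. The table of working groups in section {5d} assigns the recording and reporting of events to the day-to-day management team, which consists of the principal investigator and main researchers.

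The reporting window stands under Provisions for post-trial care {30}: "After informed consent for the screening has been obtained until the last follow-up visit, all adverse events causally related to a study intervention will be" reported.

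Exposure takes place in the therapy sessions. Intervention description {11a} gives "three sessions of 45 minutes upper limb therapy per week for a period of eight weeks", and states: "All therapy sessions will be performed by individual physiotherapists or occupational therapists", one child to one therapist. Under Strategies to improve adherence to interventions {11c}, "therapists from both groups will be asked to record the frequency and duration of the effective therapy time and the executed exercises/activities". The stated purpose of that record is to evaluate compliance.

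The same section adds two contacts during therapy: "After the first week of intervention and halfway through the intervention period, parents and therapists will be contacted by one of the researchers". Plans to promote participant retention {18b} repeats this for parents only: "parents will be contacted after the first week of therapy and halfway the intervention period to discuss feasibility of the therapy and the progress". Neither section says whether these contacts are in person, and neither lists adverse events as a topic.

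**The concern.** The person who sees the child at every session is not a named source of adverse event information, and the record that this person keeps is not described as having a place for it. Each element is stated in the article, but they do not join up. Section {22} relies on the family, section {11c} asks the therapist about time and content, and the two mid-therapy contacts have another purpose.

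What is at stake is harms ascertainment. Minor events in children aged 7 to 15, such as pain, skin irritation or fatigue during a session, are easily forgotten if first asked about weeks later. The causality judgement in section {22} would then rest on family recall, without an account from the observer who was present. Other safeguards are light: section {21a} sets up no data monitoring committee, on the ground that the therapy and assessments were safe in earlier studies, and section {21b} plans no interim analysis. Routine collection therefore carries much of the weight.

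**Working it through.** **Inputs.** Three sessions of 45 minutes per week for 8 weeks (section {11a}); post-intervention assessment T1 at 0 to 2 weeks after therapy ends (section {18a}); researcher contacts after week 1 and halfway (section {11c}). Week 0 is the first session. Halfway is taken as 8 / 2 = week 4, which is an assumption, since the article gives no week number.

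**The plan's own figure.** 3 × 8 = 24 sessions per child; 24 × 45 min = 1,080 min = 18 hours. The article states "resulting in a total therapy duration of 18 hours", so the schedule reproduces.

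**Timing of T1.** Earliest 8 + 0 = week 8; latest 8 + 2 = week 10.

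**Delay until an event is asked about.** The article states no such interval. It depends on what counts as a participant contact and on whether the two mid-therapy contacts raise adverse events.

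| Reading | Points of enquiry (weeks) | Gaps (weeks) | Longest |
|---|---|---|---|
| A. Only the assessment visits count | 0, then 8 to 10 | 8 to 10 | 8 to 10 weeks |
| B. The week-1 and halfway contacts also elicit events | 0, 1, 4, then 8 to 10 | 1; 3; 4 to 6 | about 6 weeks |
| C. Therapy sessions count as participant contacts | every session | on average 7 / 3 = 2.3 days | days |

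In reading A the longest delay applies to an event at the first session; an event at the last session is asked about 0 to 2 weeks later. In reading B the longest gap runs from week 4 to T1 at week 10: 10 − 4 = 6.

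**Which reading the text supports.** None is fixed.

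- Reading A takes literally the in-person mode in section {22} and the stated purpose of the contacts in section {11c}.
- Reading B needs the contacts to cover a topic that neither section names.
- Reading C needs the therapist to hold the conversation and relay it to the research team. No section gives the therapist that task, though none rules it out.

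Under all three readings, the therapist has no stated duty to record or pass on an event.

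**The case against.** The strongest reply has four parts.

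1. *Participant contact is undefined.* Sessions are in person and three times a week, so they could be meant. This stands. A reader might infer that in-person collection happens only at screening, T0, T1 and T2, and that events during therapy are captured by recall up to 10 weeks later. The documents do not say so; 8 to 10 weeks is the worst case of three.

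2. *Therapists are contacted.* Section {11c} has a researcher contact them, as well as parents, after week 1 and halfway. Pain, fatigue or refusal could well come up when feasibility is discussed. This also stands, so it would be wrong to say that the trial never speaks to the observer at the session. It narrows the gap but does not close it, because no adverse event question is stated.

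3. *The article is condensed.* Forms and reporting duties may stand in the full protocol, and section {22} does not bar therapist reports. It would therefore go too far to say that children and parents are the only source the trial will use. But the article is not silent here: it chose to state source, mode and occasion for events, and content for the log. The point concerns what it states.

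4. *No harm to the results is shown.* This stands. One could multiply 24 sessions by 50 children to get 1,200 sessions without a described adverse event entry, but that counts planned exposure, and the documents give no event rate. The long interval between T1 and T2 likewise does not measure missed events, since study therapy has ended by then. The described method is the same in both arms, and neither the objectives nor Table 1 includes a harms endpoint.

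**Conclusion.** The point holds as a cheap improvement of low severity. Section {22} names participants and parents, in person, as the source of adverse event information. It leaves out the therapists who deliver all 24 sessions, whose described log covers time and content. The two mid-therapy contacts, which do include therapists, are not stated to ask about events.

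The delay before a first-session event is asked about is 8 to 10 weeks if neither the contacts nor the sessions serve this purpose. The longest gap is about 6 weeks if the contacts do, and days if the sessions do. These figures rest on T1 falling 0 to 2 weeks after an 8-week course and on halfway meaning week 4.

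A reader should not infer that events have been or will be missed in any particular number, that the arms are treated differently, or that the efficacy conclusions are affected. What is shown is that the stated method is weaker than one available at almost no cost, in a paediatric trial without a data monitoring committee.

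**What to change.** Amend sections {22} and {11c}, with the same wording for both arms:

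1. Add a per-session adverse event entry (none / describe) to the existing therapist log, and have the therapist pass any event to the day-to-day management team. Name the therapist as a source in section {22}.
2. Ask parents and therapists one fixed adverse event question at the week-1 and halfway contacts, whether or not these are in person, and align section {18b}.
3. State what a participant contact is, so that the reader can tell whether sessions count.

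Optionally, put the same item on the questionnaire about upper limb therapy that section {11d} already plans for parents and physiotherapists over the follow-up period.

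The cost is one line on a log already in use and one question at two contacts already planned. The downside is a slightly longer log and more minor events to record and assess. Identical sources in both arms keep event counts comparable. Section {25} provides the amendment route, and recruitment may run to 30 June 2027, so children still to be enrolled could be covered. If the full protocol already contains these elements, a sentence in section {22} saying so is enough.

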### Frequency and plans for auditing trial conduct {23}

First, to comply with the sponsor responsibilities related to study monitoring, UZ/KU Leuven has appointed the Clinical Trial Center (CTC), who is not involved in the execution of clinical studies, to perform audits on UZ/KU Leuven-sponsored studies. These audits are organized following a risk-based approach. Secondly, general trial conduct will be evaluated by the day-to-day management team. These evaluations include source data verification, follow-up of issues during data collection, and validation of missing data. The day-to-day management team will further submit a yearly progress report to the Ethics Committee Research UZ/KU Leuven, according to the regulation of good clinical practice (ICH-GCP). Lastly, the researchers will permit study-related monitoring, audits, ethical committee review, and regulatory inspection by any competent authority, providing direct access to all related source data and/or documents.

### Plans for communicating important protocol amendments to relevant parties (e.g., trial participants, ethical committees) {25}

If important protocol modifications are required, a valid and substantial amendment will be prepared by the principal investigator, upon consultation of the trial steering group. This amendment will be submitted to the Ethics Committee Research UZ/KU Leuven for approval. When ethical approval is obtained, the protocol registration at ClinicalTrials.gov will be updated using tracked modifications. Any changes compared to the initial protocol will further be pointed out in scientific publications of the study results.

### Dissemination plans {31a}

The results of this study will be disseminated by peer-reviewed journal publications as well as active participation at international conferences. Authorship of publications will be determined in accordance with the guidelines of KU Leuven and in accordance with the requirements of the respective (medical) journal. We will further participate in activities and events that focus on science communication to a non-expert audience, including parents, children and adolescents with and without disabilities and clinicians.

## Discussion

This study aims to investigate the efficacy of somatosensory discrimination therapy and dose-matched motor therapy to improve sensorimotor upper limb function in children and adolescents with uCP who present with tactile impairments. We will further investigate the potential role of different behavioral and neurological predictors of therapy response. Our main hypothesis is that somatosensory discrimination therapy will result in improved bimanual performance at follow-up, compared to dose-matched motor therapy.

A comparable trial protocol has been published in 2018 by McLean and colleagues [58]. However, due to difficulties with recruitment during the COVID19 period, earlier discontinuation of this trial was necessary. As only six children with uCP had completed the intervention, preliminary analysis of the trial results was impossible. Nevertheless, their earlier feasibility study has shown that Sense for Kids is a feasible and engaging therapy for children and adolescents with uCP [41, 42].

Despite the fact that somatosensory function has shown to be critical to coordinate and finetune movements of each hand separately to a skilled bimanual performance [1], therapy programs that specifically target the somatosensory impairments are scarce. To the best of our knowledge, this is the first RCT comparing the effectiveness of an intervention approach specifically designated to address somatosensory impairments to a dose-matched motor therapy in children and adolescents with uCP that present with tactile impairments in the upper limb. Although there is favorable evidence for this therapy concept to improve upper limb function in adult stroke patients [28, 33, 34]. Sensorimotor upper limb function will be comprehensively evaluated using clinical assessments that have shown to be valid and reliable in children and adolescents with uCP, as well as based on robotic evaluations and instrumented three-dimensional motion analysis.

Gaining insight in how somatosensory discrimination therapy impacts upper limb function might be important to improve current upper limb therapies specifically for children and adolescents with uCP who present with tactile impairments. If targeting somatosensory impairments in the upper limb could lead to a breakdown of the vicious circle of somatosensory impairments, reduced use of the impaired upper limb during bimanual activities, and reduced developmental experience, this therapy could result in improved functional independence and quality of life. By investigating potential predictors of therapy response, the results of this study may aid in further individualization of upper limb therapy.

## Trial status

Recruitment started on August 8, 2023. The anticipated end-date of recruitment is 30 June 2027 or when the total number of 50 participants is reached. The trial will be conducted according to the protocol (version 5.2 – 19 January 2024) for which ethical approval was obtained.

## Data Availability

The de-identified dataset will be made publicly available upon publication of the study results via KU Leuven Research Data Repository.

## Abbreviations

CP: Cerebral palsy
uCP: Unilateral cerebral palsy
RCT: Randomized controlled trial
mHFCS: Modified House Functional Classification System
COPM: Canadian Occupational Performance Measure
AHA: Assisting Hand Assessment
MACS: Manual Ability Classification System
GAS: Goal Attainment Scaling
CBCL: Child Behavior Checklist
Ad-AHA: Adolescent Assisting Hand Assessment
CHEQ: Children’s Hand-use Experience Questionnaire
ETH MIKE: ETH Motor Impairment and Kinesthetic Evaluation
MRI: Magnetic resonance imaging
dMRI: Diffusion-weighted imaging
MRICS: MRI classification system
sqMRI: Semi-quantitative MRI scale
